## Abstract

**Background:**

People who overdose on opioids when they are alone or unmonitored are at heightened risk of death as other people do not know they should provide an emergency response. Wearable technology provides an opportunity to continuously measure respiratory function and ultimately send an alert if respiratory depression occurs.

**Objective:**

This study evaluates the feasibility and acceptability of PneumoWave DC in UK homeless hostels or supported accommodation settings (equivalent to Housing First in the USA) for individuals at high risk of opioid overdose. The PneumoWave system consists of a wearable biosensor that is affixed to the chest and records chest motion and which, in future, could potentially provide early detection of respiratory depression and trigger overdose response.

**Methods:**

RESCU-2 is a non-randomised, observational trial conducted in supported accommodation facilities across the UK. 50 participants who currently use opioids and live in homeless hostels in England and Scotland will wear the PneumoWave biosensor for varying periods to collect data over 2,000 participant-days. The biosensor will be linked via Bluetooth to a hub for continuous respiratory data collection. Self-reported drug use during the trial will be measured using drug diaries. Quantitative acceptability data will be measured using structured satisfaction surveys, while qualitative acceptability data will be obtained from interviews and focus groups with both residents and staff. Statistical analysis will include descriptive evaluation of feasibility outcomes, while qualitative data will undergo thematic analysis. The primary objectives of the study are: 1) feasibility of the study protocol within the hostel setting; 2) acceptability and usability of the device among people who use opioids and live in hostels; 3) acceptability of the device among staff who work in hostels and respond to overdose events. Primary outcomes are recruitment, total hours of usable data collected and successful recording of key outcome measures, among others. Trial registration: ISRCTN12060022.

**Results & Significance:**

Findings will inform the feasibility of future integration of chest biosensor technology into hostel settings, assessing participant adherence, usability, and acceptability among people who use substances and staff. Insights gained will support the design of future trials and further development of remote monitoring technologies for overdose prevention and response strategies.

## Introduction

Opioid-related overdose is a major public health crisis, with overdose deaths increasing globally. According to the United Nations Office on Drugs and Crime (UNODC), over 100,000 opioid-related deaths occur worldwide each year, with mortality rates rising due to the increased prevalence of synthetic opioids such as fentanyl [1,2]. In the UK alone, opioid-related deaths have reached record levels [3]. Scotland has experienced particularly high rates, with 1,172 drug-related deaths recorded in 2023, making it one of the highest per capita drug death rates in Europe [4]. People experiencing homelessness tend to have high levels of opioid use and co-existing physical health problems and are at particular risk of overdose [5–8]. Traditional harm reduction approaches, including supervised drug consumption facilities and naloxone distribution, have been introduced as initiatives to reduce overdose mortality [9–11]; however, their reach remains limited due to geographic, legal, and social barriers. Given these limitations, emerging digital health technologies, such as biosensors for real-time respiratory monitoring, present an innovative approach to overdose prevention by providing continuous physiological data that may enable early intervention before fatal respiratory depression occurs.

PneumoWave DC is a wearable biosensor system designed to monitor chest motion. Future versions will aim to detect respiratory depression in individuals at high risk of overdose. The DC system comprises a small chest-worn biosensor that transmits real-time chest motion data to a Hub, the device is designed to be unobtrusive, allowing for prolonged use without discomfort. In future developments the device will be capable of providing real-time alerts when chest motion abnormalities potentially linked to opioid use are detected.

Previous research has demonstrated that wearable biosensors have significant potential for improving health monitoring in various medical contexts, including respiratory diseases such as chronic obstructive pulmonary disease (COPD) and sleep apnoea. Other studies have investigated the use of technologies for opioid-induced respiratory depression, more specifically, studies testing various sensors and devices highlight the potential for wearable real-time monitoring for overdose prevention [12–14]. However, despite these advancements, the practical application of biosensors for harm reduction remains understudied. Most research to date has been conducted in controlled environments such as hospitals or supervised injection sites, leaving a gap in understanding how these devices perform in real-world, community-based settings. This study, RESCU-2, aims to bridge that gap by evaluating the feasibility and acceptability of PneumoWave Biosensor within homeless hostel or supported accommodation environments (equivalent to Housing First in the USA) where individuals may use opioids in private, unsupervised conditions. Supported accommodation facilities provide an opportunity to implement life saving interventions when notified in environments where individuals are already receiving services and support. This study builds upon findings from the RESCU-1 study which explored the feasibility of respiratory monitoring in people recruited in treatment clinics and needle exchanges, and who self-report their drug use.

This study aims to evaluate the feasibility, acceptability, and technical implementation of a wearable biosensor (PneumoWave DC system) to record chest motion in individuals at risk of opioid overdose living in supported accommodation.

The primary objectives are to:

Assess the feasibility of implementing the study protocol within supported accommodation settings. This includes recruitment and retention of participants, adherence to study procedures, and overall completeness of data collection.Evaluate the acceptability and usability of the biosensor system among residents who use opioids. This will be informed by participant engagement, qualitative feedback, and satisfaction survey responses.Assess the acceptability of the biosensor system among hostel staff and key stakeholders, particularly those involved in overdose response.Determine the technical feasibility of capturing chest motion data using the PneumoWave DC system in this setting, and evaluate its potential to contribute to overdose detection algorithm development.

Secondary objectives include:

Descriptive analysis of events where sensor data corresponds to suspected opioid overdose episodes, based on staff reports or participant accounts.Evaluation of the system’s ability to detect changes in recorded chest motion during suspected events and to differentiate overdose-related respiratory suppression from typical patterns.Exploratory comparison of biosensor traces from overdose and non-overdose periods to assess system sensitivity and specificity in identifying overdose events.

## Methods

### Study design

RESCU-2 is a non-randomised, observational feasibility study designed to assess the implementation of a wearable (PneumoWave DC) biosensor system in supported accommodation facilities. The study combines quantitative and qualitative methods to evaluate feasibility, acceptability, and data capture. It builds on the RESCU-1 study, which explored biosensor use among individuals accessing needle exchange services and self-reporting drug use in community settings. In contrast, RESCU-2 is focused on individuals living in hostels and supported accommodation, including both short- and long-term residents, where unsupervised drug use and overdose risk are common.

### Setting and participants

The study is conducted at multiple supported accommodation sites across England and Scotland (Fig 1). These organisations provide housing and support services for individuals who experience homelessness or are at risk of drug-related harm, including opioid overdose. The participating sites are selected based on their capacity to facilitate harm reduction interventions and their history of working with individuals with substance use disorders.

**Fig 1 pone.0326482.g001:**
[figure not shown]
A hostel room in London (left) and Glasgow (right).

There are no exclusions based on length of stay, and both short- and long-term residents are eligible. Participants are enrolled on a rolling basis. Although it must be noted that while the protocol initially includes both short- and long-term residents, current ongoing recruitment has focused solely on longer-term residents, following feedback from participating services that overnight residents are difficult to identify and engage reliably for research participation.

Accommodation staff play a key role in participant recruitment and data collection. Staff members will identify eligible individuals based on inclusion criteria and will introduce them to the study during routine interactions, such as welfare checks and scheduled support meetings. Potential participants will receive an overview of the study’s aims and procedures before providing informed consent (Fig 2). Staff will also assist in data collection by documenting participant engagement with the biosensor, noting any relevant observations, and supporting the administration of surveys and qualitative interviews.

**Fig 2 pone.0326482.g002:**
[figure not shown]
Schedule of procedures. SPIRIT checklist (S1 File) is included as a supplementary file.

50 participants will be recruited over 6–8months to collate 2,000 participant-days of sensor data. Each participant is expected to wear the device for 4 weeks or longer. Recruitment will be conducted on a rolling basis, with eligible participants invited to enrol throughout the study duration.

Staff will maintain a log of recruitment efforts, including reasons for non-participation when applicable, to assess barriers to engagement. This approach ensures that data collection reflects real-world conditions and allows for flexibility in accommodating the needs of a transient and vulnerable population.

### Participant payment

Participants will receive £25 supermarket voucher per week if they show evidence of wearing the sensor and the Hub remains in situ in their residence. Participants will also receive £20 for taking part in a semi-structured interview and £10 for participation in a focus group.

Inclusion criteria:

Residents of participating supported accommodationsAged 18 or aboveCurrent use of any opioids (e.g., heroin)Willingness to wear biosensorAbility to provide informed consent

Exclusion criteria:

Severe cognitive impairment preventing informed consentMedical contraindications to biosensor use (e.g., severe dermatological conditions preventing adherence of the device)

### Participant recruitment and enrolment

Potential participants will be identified by accommodation staff and provided with information about the study. Those expressing interest will undergo an informed consent process before enrolment. No formal screening process will be implemented beyond staff assessment and participant self-reporting of opioid use. Consent for satisfaction surveys and interviews will also be sought at the enrolment stage.

### Study procedures

Each participant is issued the PneumoWave DC system (Fig 3), comprising a small, chest-worn biosensor and a local data collection Hub. The device captures motion in three dimensions (x, y, z), which is converted into respiratory rate and waveform data. Data are continuously transmitted to a secure, cloud-based platform via the Hub.

**Fig 3 pone.0326482.g003:**
[figure not shown]
Image of Pneumowave chest sensor and location of placement on the body.

Participants are asked to wear the biosensor as consistently as possible during their stay in the hostel. They are not required to wear it outside the facility. Hostel staff assist with basic maintenance, including support for battery replacement and electrode changes. Staff and participants are provided with brief training and written guidance.

Upon enrolment, participants will receive a wearable biosensor that monitors chest motion and transmits data to a Hub. The study procedures include:

Demographics and baseline assessment: collection of age, gender, health status (including respiratory conditions) and opioid use history (abbreviated AIR tool [15,16].Biosensor data: duration worn, number of useable hours recorded, signal qualityDrug use diary: participants will self-report drug use via a confidential diary.Overdose reporting: any overdose events observed or reported are documented by hostel staff using a structured formSatisfaction surveys: A brief questionnaire administered to participants to capture perceptions of comfort, usability, and willingness to use the device long term. At least one survey will be completed by each participant to assess usability and comfort, at 4 weeks.Qualitative interviews and focus groups: will be conducted with participants and staff to explore experiences, perceived benefits, and challenges of using the technology.

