#### Quantitative measures.

Approximately four weeks after enrolment, a subset of participants and hostel staff are invited to take part in semi-structured interviews. These explore perceptions of the biosensor’s usability, comfort, acceptability, and perceived value. A topic guide will be used and adapted iteratively. Interviews are audio recorded, transcribed, and anonymised for analysis. Where feasible, focus groups are also conducted with staff to explore operational perspectives and overdose response integration.

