#### Qualitative interviews.

To explore participant experiences and perceptions of the PneumoWave DC system, semi-structured qualitative interviews will be conducted approximately four weeks after the initiation of data collection. These interviews will provide insights into usability, acceptability, and any challenges encountered while using the biosensor. A structured topic guide will be used to ensure consistency across interviews while allowing for open-ended responses (Supplementary File). This guide will include questions on ease of use, perceived benefits, privacy concerns, and the impact of the biosensor on participants’ daily lives.

Interviews will be conducted face-to-face in a private setting within the supported accommodation facility to ensure confidentiality and participant comfort. Interviews will be audio-recorded with consent from the participant and transcribed verbatim for thematic analysis. Focus groups or interviews with accommodation staff will also be conducted to gather perspectives on the feasibility of implementing the biosensor within supported housing environments. These discussions will explore staff experiences with participant recruitment, device adherence, and any operational challenges that arose during the study.

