### Ethical and safety considerations

The study is conducted in accordance with Good Clinical Practice (GCP) guidelines and has received ethical approval from the appropriate Research Ethics Committee (REC) from the University of Dundee (UOD-SMED-SLS-Staff-2024-24-107). The Sponsor for the study is University of Dundee.

Written and informed consent will be taken from all participants prior to any study procedures, including both sensor deployment and participation in interviews. Consent is taken by trained research staff or hostel staff and is treated as an ongoing process. Participants have the right to withdraw at any time without consequences. A sample consent form is included as a Supplementary File.

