### Status and timeline

This study is part of a 12-month funded study. Funding started in September 2024, when approvals were sought and sites were set up from September to December 2024. The first participant was recruited on 28 January 2025 and is ongoing. Recruitment and data collection will continue until 31 July 2025. Data analysis and results have not yet been generated. Data analysis and results are expected in August 2025 with the final report expect to be completed by 31 August 2025, with dissemination following thereafter.

Although the original protocol included the possibility of enrolling short-term or overnight residents, and this is described in the manuscript, early consultation with participating services indicated that identifying and engaging this group in a meaningful way would not be feasible. As a result, recruitment has focused exclusively on longer-term residents, who are more stable and accessible for follow-up and data collection.

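### The resident survey and interviews have about 4 weeks as their only stated time point, so residents who leave or withdraw sooner are likely to be missed and acceptability may be over-estimated

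*Protocol article*

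**What the plan says.** The protocol article gives one time for the resident survey (Study procedures): "At least one survey will be completed by each participant to assess usability and comfort, at 4 weeks". It gives much the same time for interviews, in two places. Under Quantitative measures: "Approximately four weeks after enrolment, a subset of participants and hostel staff are invited to take part in semi-structured interviews". Under Qualitative interviews: "semi-structured qualitative interviews will be conducted approximately four weeks after the initiation of data collection".

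Survey responses and qualitative feedback are both listed under Study outcomes as components of the primary acceptability and usability outcome.

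On how long residents stay in the study, Setting and participants says: "Each participant is expected to wear the device for 4 weeks or longer". The same section speaks of flexibility in "accommodating the needs of a transient and vulnerable population". Ethical and safety considerations adds: "Participants have the right to withdraw at any time without consequences". Status and timeline reports that "recruitment has focused exclusively on longer-term residents".

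The text describes no survey or interview when a resident stops wearing the sensor, withdraws or moves out. The staff log of reasons, in Setting and participants, concerns people who do not take part at recruitment.

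**The concern.** The two instruments that collect residents' own views share one time point, so neither fills the other's gap. Week 4 is also the end of the minimum expected wearing period. A resident who leaves or withdraws before then has no stated occasion on which to be asked, yet the text expects a survey from everyone enrolled. The two statements fit together only if nobody is lost in the first four weeks. The article does not assume that: it makes retention an outcome and allows withdrawal at any time.

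If those lost early like the device less than those who remain, the acceptability result describes the remaining group and reads too favourably. First-hand reasons for giving up, which matter a good deal to a feasibility study, would be the hardest information to recover. The incentives do not help. Under Participant payment the weekly voucher depends on evidence of wear, and no payment is stated for completing the survey.

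**Working it through.** **Plan's own figures.** The article states no expected drop-out, satisfaction rate or acceptability threshold, so there is no figure to reproduce. A side check of exposure is consistent. The target is "2,000 participant-days of sensor data" from 50 participants, or 2,000 / 50 = 40 days each on average, against a minimum of 50 × 28 = 1,400 days at four weeks each. This says nothing about how many residents are lost before week 4.

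**Who has a stated occasion to be asked, reading the passages together.**
- Still resident and wearing at week 4: survey, and possible interview.
- Still resident but no longer wearing: also reachable. The survey is planned for every participant, and the interview clock runs from enrolment or from the start of data collection. Neither is tied to continued wear.
- Withdrawn or moved out before week 4: no occasion described.

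The gap is therefore firmest for the third group.

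**Size, under assumptions.** Let d be the share of enrolled residents lost before week 4 and not surveyed, a the proportion satisfied among those surveyed, and b the proportion satisfied among those missed. A yes/no rating is used only for illustration; the article defines no such endpoint.

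- Value in all enrolled = (1 − d)a + d·b
- Value observed = a
- Over-estimate = a − [(1 − d)a + d·b] = d(a − b)

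All values of d, a and b are assumed. With a = 80%, the over-estimate in percentage points is:

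| d | Surveyed, 50(1 − d) | b = 20% | b = 40% | b = 60% | b = 80% | 95% half-width |
|---|---|---|---|---|---|---|
| 10% | 45 | 6 | 4 | 2 | 0 | 11.7 |
| 20% | 40 | 12 | 8 | 4 | 0 | 12.4 |
| 30% | 35 | 18 | 12 | 6 | 0 | 13.3 |
| 40% | 30 | 24 | 16 | 8 | 0 | 14.3 |

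Example: d = 30%, b = 40% gives 0.30 × (0.80 − 0.40) = 0.12. The half-width is 1.96 × √(0.80 × 0.20 / n); at n = 40 it is 1.96 × √0.004 = 12.4 points. With b = 40%, the over-estimate stays below sampling error up to 30% loss and exceeds it at 40%.

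**Effect of reaching some of them.** If half of those otherwise missed were surveyed (a = 80%, b = 40%), the observed value is [(1 − d)a + 0.5·d·b] / [(1 − d) + 0.5·d]. At d = 30% this is (0.56 + 0.06) / 0.85 = 72.9%, against 68% in all enrolled, an over-estimate of 4.9 points instead of 12. For d = 10, 20 and 40% the figures are 1.9, 3.6 and 6.0 points instead of 4, 8 and 16.

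**The case against.** A reader might infer that residents who stop wearing the sensor are never asked. The text does not support that. It plans at least one survey for every participant and limits neither instrument to current wearers, so a stopper who still lives in the hostel can be reached at week 4.

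A reader might also infer that early rejection of the device would leave no trace. That is too strong as well. Retention, wear time, diary completion and operational problems are primary outcomes. Staff record engagement and observations (Setting and participants), and staff interviews or focus groups cover adherence (Qualitative interviews). Early stopping would be counted and staff could report reasons. What is lost is the residents' own account.

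Three further points reduce the risk or the certainty:
- Confining recruitment to longer-term residents should lower early departure, although it does not remove it and does not prevent withdrawal.
- People who move for housing reasons need not dislike the device, so an upward bias is plausible but not established.
- The schedule of procedures is a figure that was not available for this review, and the full protocol may describe an exit contact.

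Limitations of study design already says in general terms that variable engagement may bias results.

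These objections narrow the point without removing it. Followed as written, the text gives no occasion to hear from those who leave or withdraw before week 4. If an exit contact exists elsewhere, the article's description of survey and interview timing should mention it.

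**Conclusion.** The concern holds in a limited form. A survey from every participant is promised, its only stated time is 4 weeks, and no survey or interview is described at withdrawal or departure. Residents who leave or withdraw before week 4 are likely to be missed by both resident instruments, and a primary outcome may be over-estimated as a result.

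The size cannot be determined from the document. With 80% satisfied among those surveyed and 40% among those missed, it would be 4 to 16 points over 10 to 40% early loss. With 60% among those missed it would be 2 to 8 points, and with equal ratings it would be zero. These figures assume that nobody lost early is surveyed. It would go too far to say that acceptability is biased upward, because both the drop-out rate and the difference in satisfaction are assumed.

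**What to change.** - **Survey timing.** Give the same questionnaire at 4 weeks or at device stop, withdrawal or notice of departure, whichever comes first.
- **Reporting.** Give the number of responders out of all enrolled, and show responses separately for those who did and did not complete 4 weeks.
- **Interviews.** Choose the planned subset purposively so that it includes early stoppers and low wearers.

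Counting non-responders as finding the device unacceptable is not recommended. It presupposes a yes/no endpoint that the article does not define.

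The cost is a minor amendment. The questionnaire, the staff and the number of interviews stay the same, and consent for surveys and interviews is already sought at enrolment. Early stoppers would answer after shorter exposure, so days since enrolment should be recorded with each survey. Residents who leave without notice would still be missed, so the change reduces the gap without closing it.
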